### Activities in control CAPs

No external intervention is planned for control clinics, although enhanced monitoring, surveillance and data collection will occur at all facilities during the trial. We will carefully monitor control facilities and their catchment areas to limit the risk of contamination. Contact with referral hospitals and outcomes of referred cases will also be carefully considered, as we anticipate that in both intervention and control facilities complicated cases will be transferred to the same referral hospitals. Additionally, we hope to provide all clinicians involved in labor and delivery with PRONTO training upon study completion and the messages and material developed in the social marketing component.

### Main outcomes and measures

This implementation project aims to directly impact perinatal health (Table 1), thus the primary outcome is the change in mean PMR (deaths occurring between 28 weeks gestation to 7 days, per 1,000 live births) in intervention versus control CAPs. Process outcomes expected to contribute to reduce PMRs (via PRONTO training) include increased knowledge and self-efficacy for diagnosis and initial management of common emergencies and self established clinic goal achievement for improving care. Intermediate outcomes expect to evaluate the exposure of the audience to the social marketing campaign will be change in attitudes, knowledge and practices in relation to institution-based childbirth among pregnant women and health personnel. The other main outcome measure (expected to be impacted primarily by the social marketing campaign and TBA linkage activities) is the change in proportion of institution-based deliveries in intervention versus controls CAPs. However, attributing impact to the various elements of the intervention will not be straightforward and will require careful analysis including additional qualitative work at the completion of the study.

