**Methods/Design:**

A matched pair cluster-randomized trial will be conducted in clinics in four rural indigenous districts with the highest maternal mortality ratios in Guatemala. The individual clinic will serve as the unit of randomization, with 15 matched pairs of control and intervention clinics composing the final sample. Three interventions will be implemented in indigenous, rural and poor populations: a simulation training program for emergency obstetric and perinatal care, increased participation of the professional midwife in strengthening the link between traditional birth attendants (TBA) and the formal health care system, and a social marketing campaign to promote institution-based deliveries. No external intervention is planned for control clinics, although enhanced monitoring, surveillance and data collection will occur throughout the study in all clinics throughout the four districts. All obstetric events occurring in any of the participating health facilities and districts during the 18 months implementation period will be included in the analysis, controlling for the cluster design. Our main outcome measures will be the change in perinatal mortality and in the proportion of institution-based deliveries.

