## Methods/Design

This matched pair cluster randomized trial will assess the effectiveness of a package of three interventions that together aim to decrease perinatal mortality by increasing the proportion of institution-based deliveries: 1) implementation of PRONTO, a simulation-based program for team training and effective management of obstetric and perinatal emergencies; 2) application of a social marketing strategy to increase utilization of public sector health facilities for childbirth; and 3) strengthening the link between TBAs and public sector health services through the participation of professional midwives. The unit of randomization and the unit of analysis will be at the CAP level.

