**Figure 1 F1:**
[figure not shown]
Flow diagram of perinatal intervention package trial phases.

Given our inability to strictly control patterns of movement of women and infants between clinics, the study design includes another important step: as part of the matching process we selected CAPs that are geographically separated in such a way that it would be highly unlikely that a woman would travel to an intervention site rather than a closer facility. However such travel will be thoroughly monitored to every possible extent so as to be able to measure the resulting degree of possible contamination, if any, and take this into account in the data analysis and interpretation of results. The monitoring procedure will note the communities of residence of women delivering in the clinics. Furthermore, the study’s conservative sample size requirement will allow detection of an intervention effect even if it is mildly diluted by such experimental contamination.

Clinic supervisors and staff will not be blinded to their allocation group as they will see evidence of the social marketing campaign and be trained in the intervention group. They will remain blinded to the results until the end of the study to alleviate potential tensions that could rise in case they wish to introduce aspects of the intervention to control group CAPs. We will also emphasize to all supervisors and staff that no conclusions can be drawn regarding the possible benefit of the intervention until the study is completed.

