Two professional midwives, with experience and good communication skills will be in charge of implementing this intervention and supporting these TBA activities. Beyond the roles suggested by WHO, the professional midwives will conduct a survey to assess the activities and practices of TBAs in the districts of study. Questions like the number of deliveries assisted per month, the number of pregnant women being followed, the number of emergency obstetric references made in the last year, the number of training session during the last year, etc. will help to determine ‘Active TBA’, defined as those who assisted at least one delivery per month in the last year. Once identified ‘Active TBA’ and the professional midwives will have a close and personnel relationship and meet to discuss cases of pregnancy and delivery complications. Training simulation-based in direct causes of maternal death will be developed. TBA with close relationships with CAPs will be invited to participate in PRONTO training. Moreover, after each training simulation-based session a simple assessment, hands up, will be obtained from the session. This simple method will be allowed to identify the knowledge, attitude and practice from TBA for direct maternal death causes. The professional midwives will also provide promotional material to TBA to encourage them to bring women to the CAP for vaginal delivery prior to complications.

We expect this strategy to result in a stronger, more positive relationships between TBAs, communities and formal health services, which we hope will impact the proportion of women giving birth in clinics, especially in emergency situations.

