### Data collection, management and storage

Data collection will occur in 3 phases: 1) pre-intervention (4 months), including qualitative work to drive the social marketing campaign, and quantitative work that will establish more reliable baseline data for morbidity and mortality indicators; 2) intervention, including collection of training and social marketing process indicators, and 3) post-intervention, including monthly follow up (12 months) in clinics and communities.

Data will be obtained from a variety of sources during the pre-intervention and implementation phases at three levels: 1) community level data to determine accurate denominators in terms of overall number of births and perinatal and maternal deaths, 2) clinic level data to be collected for all included CAPs, both intervention and control for morbidity and mortality indicators and 3) data to be collected only at intervention clinics, primarily related to participants in PRONTO training. On a monthly basis, trained personnel in each district will visit all offices responsible for registering certificates of live births, and stillbirths. Information from civil registry offices and health district offices will be compared to guarantee the quality of data collected and avoid the possible sub-registration typical of remote rural areas in developing countries. Community field workers will collect local home birth and death data from community liaisons and key informants. Finally, data on clinic deliveries in the study sites and their outcomes will be collected.

All field workers will be trained in data collection procedures including the ethical treatment of data. All data will be initially collected with paper forms from the aforementioned registries and offices and be assigned individual codes to maintain individual anonymity, confidentiality and privacy. Once the needed data is extracted from the file all individual identifiers will be removed, leaving only unique codes designating clinic and patient. These then will be entered into a computerized database; a separate log to match records will be kept in a secure locked file. Paper files will also be secured in a locked file accessible only to authorized personnel trained in ethical management of confidential data. Data quality and validity will be assured through bi-monthly data entry and queries to check outlying observations and key measures.

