### Data analysis plan

The effect of the intervention will be measured as the difference between matched clinics (intervention clinic minus control clinic) in PMR change from baseline to 12 months. Negative differences will indicate lower PMRs in the intervention group, adjusted for baseline rate. A one-sample two sided *t* test with corresponding confidence interval will be used to determine whether the mean rate difference as calculated over all matched pairs is statistically different from zero. A nonparametric permutation test will also be used with an exact p-value computed using the R statistical package. We will follow the same approach for secondary outcomes on which we have appropriate baseline data.

To adjust the mean rate difference in PMR between groups for variables that show some residual imbalance after pair-matching, a multiple linear regression model will be used, with the rate difference between matched clinics as the dependent variable and variables with baseline differences between matched clinics as the independent variables. Adjusted interferences for the effect of the intervention will be estimated by calculating the intercept of the resulting regression equation and comparing it to its estimated standard error [39].

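### The births and deaths that form the primary perinatal mortality rate are not settled, and a count by clinic of delivery would be open to post-randomisation selection

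*Protocol article*

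**What the plan says.** All references are to the Protocol article.

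**Towards the clinic.** Main outcomes and measures gives the primary outcome as the change in mean PMR, "deaths occurring between 28 weeks gestation to 7 days, per 1,000 live births) in intervention versus control CAPs". Methods/Design adds: "The unit of randomization and the unit of analysis will be at the CAP level". The Data analysis plan states (the quote breaks off just before the 12-month time point): "The effect of the intervention will be measured as the difference between matched clinics (intervention clinic minus control clinic) in PMR change from baseline to".

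**Towards the catchment.** The Abstract brings in "All obstetric events occurring in any of the participating health facilities and districts". Sampling methods names women and newborns living in the catchment areas as the target population. Data collection, management and storage plans community-level counts of all births and perinatal deaths to obtain correct denominators.

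**On movement and referral.** Description of interventions says that the second and third components work by raising the share of births in institutions. Traditional birth attendants are to bring women in before complications arise, and the midwife component is also hoped to "impact the proportion of women giving birth in clinics, especially in emergency situations". Activities in control CAPs expects that in both arms "complicated cases will be transferred to the same referral hospitals" and says that outcomes of referred cases will be given careful thought. Travel between clinics is to be monitored so as to "take this into account in the data analysis and interpretation of results" (Randomization and matching procedure).

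**The concern.** Randomisation protects a comparison of populations fixed before the intervention starts. Women who deliver at a given CAP are not such a population, because social marketing and the midwife liaison aim to change who they are, and only in the intervention arm. Pair matching and subtraction of the baseline rate cannot remove a change in case mix that arises after randomisation.

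The two stated aims also push in opposite directions. Attracting uncomplicated births lowers the clinic's rate, and attracting emergencies raises it. An effective programme could look harmful, or an ineffective one beneficial. Referral adds a second route: without a rule on where a death in a referral hospital is counted, any difference in referral between arms would bias the rate.

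A smaller point is that the outcome runs to day 7, while the registry visits are described as: "trained personnel in each district will visit all offices responsible for registering certificates of live births, and stillbirths". Registrations of early neonatal death are not named there.

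**Working it through.** **Design figures.** From Sample size: mean PMR 52 per 1,000, 25% reduction, 15 pairs, two-sided 0.05, 80% power. The target difference is 0.25 × 52 = 13 per 1,000. The 15 pairs cannot be reproduced, because the SD is not given as a number. Working backwards with the normal formula, the implied SD of a pair difference is 13 × √15 / (1.960 + 0.842) = 18.0 per 1,000 (16.7 with a t test on 14 df). These are implied values, not a check. Only the 25% (13 per 1,000) is used below, as a yardstick.

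**Case-mix model.** The strata and shares are assumptions, not figures from the protocol. A fraction h of catchment births is high risk with PMR rH. The rest have rL = (52 − h·rH)/(1 − h), so the catchment PMR is 52. Each birth keeps its risk wherever it occurs. With shares fL and fH of low- and high-risk births counted at the CAP:

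CAP PMR = [(1 − h)·fL·rL + h·fH·rH] / [(1 − h)·fL + h·fH]

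Example with h = 15% and rH = 200, so rL = (52 − 30)/0.85 = 25.9:
- before (fL 10%, fH 40%): (0.085 × 25.9 + 0.060 × 200)/0.145 = 97.9
- after (fL 30%, fH 45%): (0.255 × 25.9 + 0.0675 × 200)/0.3225 = 62.3, a fall of 36%

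| Shift (fL; fH) | h 15%, rH 200 | h 10%, rH 200 | h 20%, rH 150 |
|---|---|---|---|
| Low-risk drawn in (10→30%; 40→45%) | 97.9→62.3 (−36%) | 86.2→59.0 (−31%) | 88.8→60.9 (−31%) |
| Emergencies drawn in (10→12%; 20→45%) | 71.3→95.2 (+34%) | 65.5→83.9 (+28%) | 68.3→86.8 (+27%) |
| More high-risk births referred out, not counted (20→20%; 40→25%) | 71.3→57.3 (−20%) | 65.5→55.6 (−15%) | 68.3→56.7 (−17%) |
| Equal shift (20→35%; 20→35%) | 52→52 (0) | 52→52 (0) | 52→52 (0) |

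In every cell the catchment PMR is 52 before and after.

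**Referred deaths left uncounted.** If the uncounted share of deaths rises from 10% to 30%, the recorded PMR goes from 52 × 0.9 = 46.8 to 52 × 0.7 = 36.4 (−22%). From 20% to 40%, it goes from 41.6 to 31.2 (−25%). These shares are also assumed.

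**Weight of one death.** A CAP at the inclusion minimum of seven births per month has 84 births in 12 months. At 52 per 1,000 that is 84 × 0.052 = 4.4 deaths, so assigning one death elsewhere moves its rate by 1/4.4 = 23%. A busier CAP is less sensitive.

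**Price of a residence-based rate.** Low utilization of clinic-based obstetric care gives facility shares from under 5% to 34% by district. If a 25% cut reached only facility births, with equal baseline risk at home and no change in place of birth, the catchment PMR would fall by at most 0.25 × 5% = 1.25% at the low end and by 0.25 × 34% = 8.5% at the high end.

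**The case against.** The strongest reply is that the authors probably mean the catchment. The institution-based delivery proportion is worded almost identically, as intervention against control CAPs, and it needs home births in its denominator. The baseline survey collected clinic versus home delivery for each CAP. Community births and deaths are gathered for denominators, and the stated mechanism is at population level. Naming the CAP as unit of analysis identifies the cluster, not the place of birth. All of this stands. A reader might infer that the primary outcome is fixed as in-clinic births and that the randomised comparison is therefore lost. The text does not support that, because it leaves the population open.

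A reader might also infer that the package is designed to alter referral. The protocol only expects transfers in both arms. Training in diagnosis and initial management makes a difference between arms plausible but does not state one.

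Nor do early neonatal deaths rest on informants alone. Clinic records capture perinatal deaths and neonatal referrals, and registry and health district data are compared. Crossover is also limited by choosing geographically separated CAPs.

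Finally, a condensed article may leave detailed attribution rules to a fuller document. But which births and deaths make up the primary outcome is part of its definition, and here the article's own sections point in two directions.

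**Conclusion.** The point holds as an unresolved definition with serious consequences under one of its two readings. Counted by CAP of delivery, the PMR would condition on a variable that the intervention is meant to change, and neither matching nor baseline subtraction would correct this. Under the assumed strata and shifts the artefact is −31% to −36% or +27% to +34% through attraction of births, −15% to −20% through referral of high-risk births, and −22% to −25% through uncounted referred deaths, against a target of 25%. These sizes illustrate and do not estimate: they assume no such shift in control CAPs, and the attraction artefact vanishes if all risk groups move in equally. Counted by residence, the PMR does not respond to these shifts at all.

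**What to change.** In Main outcomes and measures and in the Data analysis plan, define the primary PMR and the institution-based delivery proportion over residents of communities assigned to one CAP before launch. Count every birth and perinatal death of those residents, at home, in any CAP or in a referral hospital, in the arm of the CAP of residence, and apply the same rule to the baseline rate. Let this rule replace the promise to "take this into account in the data analysis and interpretation of results" and the open-ended wording on referred outcomes in Activities in control CAPs. Report PMR by CAP of delivery as a descriptive secondary outcome, with referred deaths attributed to the referring CAP. Add registrations of early neonatal death to the monthly registry visits as a check on clinic and informant data.

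Most of the data are already planned: residence of women delivering in clinics, civil registry data, and community births and deaths. The costs should be stated openly. A community-to-CAP list is needed, and home and hospital births must also be linked to a catchment. An effect confined to facility births is heavily diluted, as computed above. The statement that 15 pairs suffice rests on an SD across clinics and should be rechecked with the SD of the catchment PMR, which the protocol does not give.

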### Data collection, management and storage

Data collection will occur in 3 phases: 1) pre-intervention (4 months), including qualitative work to drive the social marketing campaign, and quantitative work that will establish more reliable baseline data for morbidity and mortality indicators; 2) intervention, including collection of training and social marketing process indicators, and 3) post-intervention, including monthly follow up (12 months) in clinics and communities.

Data will be obtained from a variety of sources during the pre-intervention and implementation phases at three levels: 1) community level data to determine accurate denominators in terms of overall number of births and perinatal and maternal deaths, 2) clinic level data to be collected for all included CAPs, both intervention and control for morbidity and mortality indicators and 3) data to be collected only at intervention clinics, primarily related to participants in PRONTO training. On a monthly basis, trained personnel in each district will visit all offices responsible for registering certificates of live births, and stillbirths. Information from civil registry offices and health district offices will be compared to guarantee the quality of data collected and avoid the possible sub-registration typical of remote rural areas in developing countries. Community field workers will collect local home birth and death data from community liaisons and key informants. Finally, data on clinic deliveries in the study sites and their outcomes will be collected.

All field workers will be trained in data collection procedures including the ethical treatment of data. All data will be initially collected with paper forms from the aforementioned registries and offices and be assigned individual codes to maintain individual anonymity, confidentiality and privacy. Once the needed data is extracted from the file all individual identifiers will be removed, leaving only unique codes designating clinic and patient. These then will be entered into a computerized database; a separate log to match records will be kept in a secure locked file. Paper files will also be secured in a locked file accessible only to authorized personnel trained in ethical management of confidential data. Data quality and validity will be assured through bi-monthly data entry and queries to check outlying observations and key measures.

The instruments used to collect information from CAPs will be adapted from the near miss approach used by the WHO to extract appropriate data from patient records [38]. We will collect data for all normal and complicated deliveries including cases of maternal hemorrhage, preeclampsia, sepsis, referral and prolonged stay as well as neonatal complications including perinatal death, referrals and prolonged stay. Data related to individual events at the clinic level will be collected on an ongoing basis throughout the study at intervention and control sites. All information from individual charts for complicated cases will be extracted using an instrument that removes all individual identifiers and will be stored in a locked file cabinet.

### Data analysis plan

The effect of the intervention will be measured as the difference between matched clinics (intervention clinic minus control clinic) in PMR change from baseline to 12 months. Negative differences will indicate lower PMRs in the intervention group, adjusted for baseline rate. A one-sample two sided *t* test with corresponding confidence interval will be used to determine whether the mean rate difference as calculated over all matched pairs is statistically different from zero. A nonparametric permutation test will also be used with an exact p-value computed using the R statistical package. We will follow the same approach for secondary outcomes on which we have appropriate baseline data.

To adjust the mean rate difference in PMR between groups for variables that show some residual imbalance after pair-matching, a multiple linear regression model will be used, with the rate difference between matched clinics as the dependent variable and variables with baseline differences between matched clinics as the independent variables. Adjusted interferences for the effect of the intervention will be estimated by calculating the intercept of the resulting regression equation and comparing it to its estimated standard error [39].

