#### Sample size

The perinatal mortality rate (PMR) was the primary outcome of interest informing our sample size calculation. Due to the wide variability in PMRs and the expected poor quality of existing data with likely underreporting across the four study districts, we decided to use baseline data from Alta Verapaz, the district with the largest number of participating CAPs, to calculate the standard deviation in PMRs. This choice was also justified by our interest to use districts as the primary matching factors; the district selected with the largest number of clinics, was expected to have the largest intra-district variation. Therefore, for our final sample size calculation we used the mean PMRs for all four districts (estimated to be 52 deaths per 1,000 live births according to available baseline data) and the standard deviation across clinics for Alta Verapaz. With a two-sided significance level of 0.05 and a desired power of 80%, a sample size of 15 matched pairs is sufficient to detect an expected 25% reduction in mean PMRs in the intervention group. This sample size is conservative since statistical power will be increased through the use of mean change scores from baseline as the actual outcome measure.

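### The adjusted PMR regression picks its covariates by observed baseline imbalance; with 15 pairs this usually costs precision and leaves a second result of unstated status, where a fixed adjustment for baseline PMR would serve better

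*Protocol article*

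**What the plan says.** The Data analysis plan defines the effect as the within-pair difference (intervention minus control) in PMR change from baseline to 12 months. A one-sample two-sided t test with a confidence interval "will be used to determine whether the mean rate difference as calculated over all matched pairs is statistically different from zero", and an exact permutation test accompanies it. Neither involves choosing covariates.

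The next paragraph adds a regression: "for variables that show some residual imbalance after pair-matching, a multiple linear regression model will be used", with "variables with baseline differences between matched clinics as the independent variables". The adjusted effect is read from the intercept. The only stated criterion for entry is the observed imbalance. The text does not say whether this model ranks above, beside or below the t test.

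The section describes the change score as already adjusting for the baseline rate, and Sample size adds that "statistical power will be increased through the use of mean change scores from baseline as the actual outcome measure". Under Randomization and matching procedure, clinics were matched on district, then on PMR and on live-birth volume, each split at the median, and one clinic per pair was allocated at random.

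**The concern.** Randomisation within pairs makes any remaining baseline difference a chance event. A variable can be imbalanced and unrelated to PMR change, or balanced and strongly related to it. Selecting on imbalance therefore admits variables that explain nothing and omits variables that would reduce the residual variance.

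With 15 differences there are 14 degrees of freedom, and each covariate takes one. In addition, a covariate chosen because its mean difference lies far from zero inflates the standard error of the intercept, which is the treatment effect.

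Two things are at stake: the precision of the adjusted estimate, and the reading of the trial if the t test and the regression disagree and nothing says which counts.

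**Working it through.** **Inputs from the protocol (Sample size).** The design statement is: "With a two-sided significance level of 0.05 and a desired power of 80%, a sample size of 15 matched pairs is sufficient". The effect it targets is a fall of one quarter in the mean PMR. That mean is "estimated to be 52 deaths per 1,000 live births according to available baseline data", so the target difference is 0.25 × 52 = 13 per 1,000. The variability used is "the standard deviation across clinics for Alta Verapaz", whose value is not printed, so the 15 pairs cannot be reproduced. Back-solving with the noncentral t on 14 df, 80% power needs a difference of 0.776 SD, so the SD of the pair difference is 13 / 0.776 ≈ 16.7 per 1,000. The comparisons below are calibrated to that 80%.

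**Assumptions.** Baseline/follow-up correlation r of the pair differences (equal SD s at both times), number of candidate covariates, and imbalance threshold. None is given in the document. Any narrowing of the baseline differences by matching on PMR is not modelled.

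**1. What the change score leaves behind.** Its SD is s√(2(1 − r)), and its correlation with the baseline difference is −√((1 − r)/2). At r = 0.5 these are s and −0.5. A change score fixes the baseline slope at 1. Estimating the slope instead leaves a fraction (1 + r)/2 of the change-score variance, which is 0.75 at r = 0.5.

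**2. Price of a covariate.** With one covariate the intercept variance is multiplied by 1 + t²/(n − 1), where t is that covariate's own paired t statistic for imbalance. For a covariate fixed in advance the expected factor is 1 + 1/(n − 3) = 13/12 ≈ 1.08. For one admitted by a rule, the factor is at least:
- |t| > 1: 1 + 1/14 ≈ 1.07
- p < 0.10 (t = 1.761): 1 + 3.10/14 ≈ 1.22
- p < 0.05 (t = 2.145): 1 + 4.60/14 ≈ 1.33

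At p < 0.10 the covariate must explain more than 1 − 1/1.22 ≈ 18% of the variance (correlation above about 0.43) just to break even, before the lost degree of freedom.

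**3. Simulation at r = 0.5.** 15 pairs, 8,000 to 10,000 replicates per setting; one candidate is the baseline PMR difference and the others are non-prognostic.

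| | 3 candidates | 6 candidates |
|---|---|---|
| Power, unadjusted t test | 80% | 80% |
| Power, fixed adjustment for baseline PMR | 87% | 87% |
| Power, selected by abs(t) > 1 | 76–77% | about 68% |
| Power, selected by p < 0.10 | 77% | 72–74% |
| Type I error, selected regression alone | about 4% | about 4% |
| Type I error, either result significant | 5.7–6.7% | 6.0–7.2% |

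On average 1.0 and 0.3 covariates enter with three candidates under the two rules, and 2.0 and 0.6 with six.

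**4. When the rule does not lose.** With one strongly prognostic candidate (0.6–0.8), selection gives 80–81% under a p < 0.05 rule and 83–86% under p < 0.20. With five weakly prognostic candidates (0.3) plus baseline PMR, it gives 77% and 75%.

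**5. Fixed adjustment over r, change-score test held at 80%.**

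| r | 0.3 | 0.5 | 0.7 | 0.8 | 0.85 | 0.9 | 0.95 |
|---|---|---|---|---|---|---|---|
| Power | 91% | 87% | 83% | 81% | 79.5% | 78.5% | 77.6% |

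Steps 1 and 2 agree: (1 + r)/2 × 13/12 = 1 at r = 0.846, slightly lower after the lost degree of freedom.

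**The case against.** The strongest reply is that the main analysis is sound. The t test and permutation test are fixed, involve no selection, and keep their power and type I error. A reader might infer that the trial itself loses power or that its primary test is inflated; the document does not support either. A reader might also infer that covariates are picked after seeing outcomes. The trigger is baseline difference, and baseline PMR, delivery volume and proportion of clinic-based deliveries were collected for matching, so selection could be done before any 12-month result exists. Selection on baseline alone does not inflate the regression's own error.

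Nor does the text say that the more favourable of the two results will be reported. The 5.5–7% applies only if someone does that, and a fixed model kept beside the t test without a stated rank would leave the same opening. This stands, and is why the fix must name the primary analysis.

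The size of the loss also depends on assumed candidates; with three it is 3 to 4 points under the thresholds tabulated.

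Finally, a covariate list, threshold and cap may be left to a full analysis plan, so their absence is not the point. The imbalance trigger is printed, however, and a later plan with fixed covariates would have to replace it.

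**Conclusion.** The point holds for the adjusted analysis only. Choosing covariates by observed imbalance is a poor stated method with 15 pairs. It usually lowers precision, by about 3–4 points of power with three mostly non-prognostic candidates and 6–12 with six at r = 0.5, though a strongly prognostic selection can remove the loss. It also produces a second estimate of unstated status.

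A fixed adjustment for baseline PMR is better unless r is very high. It should not be read as free: it takes 1–2 df, and it loses about 2 points when r is well above 0.85. The document does not give r, but its figures make very high values doubtful if PMR is computed on clinic births. A clinic at the minimum of seven births a month has 28 births in the 4-month baseline, 28 × 0.052 ≈ 1.5 expected deaths, and a Poisson SD of √1.46 / 28 ≈ 43 per 1,000. Larger clinics or community denominators would reduce that noise and the gain.

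**What to change.** Replace the imbalance trigger with a fixed model: regress the within-pair difference in PMR change on the within-pair difference in baseline PMR, with at most the within-pair difference in log birth volume added, and test the intercept on 13 (or 12) df. Both variables were collected for matching. State which of the t test and this model is primary and label the other supportive. Report baseline imbalances descriptively only. The cost is a sentence or two in the analysis plan and 1–2 degrees of freedom; no new data are needed.
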